### Self-reported outcomes

In the current study, the CAIT and FAAM will be used to assess self-reported function. As a reliable questionnaire scale, the CAIT has been widely used to assess ankle instability for individuals with CAI [72]. Similarly, the Chinese version of the FAAM has also been tested and found to be valid [73]. These two measures will be performed using the paper version.

### Sample size

The needed sample size is calculated using the G-power software (version 3.1.9). The effect size is determined based on the value (0.35) previously reported in a study investigating cortical adaptations after balance training [40, 56]. Other parameters in the software of G-power are α error (0.05), power (0.8), number of groups (4), and number of measurements (3) [74]. Based on the above parameters, the total sample size given by the software is 64. Considering a 20% dropout rate, a total of 80 participants will be included, with 20 in each group.

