### Statistics analysis

As all outcomes are continuous variables, they will be presented as mean ± standard deviation. The normality of variables will be tested by the Shapiro–Wilk test. All statistical analyses will be carried out using the SPSS software (Version 22.0, IBM Corp., Armonk, NY, USA) and *p* < 0.05 will be considered as a significant difference. Bonferroni adjustment will be performed in post-hoc analysis when statistical significance is found. A 1-way ANOVA analysis will be conducted to compare outcomes among the four groups. Pearson's correlation coefficient will be calculated to evaluate the relationship between alterations in sensorimotor function and plastic changes in the brain. The effect size (Cohen’s d, 95% confidence intervals) will be calculated to evaluate the magnitude of difference among groups. Ranges 0.2–0.49, 0.5–0.79, and > 0.8 are considered as small, medium, and large effect sizes respectively. A 2-way repeated-measure ANOVA analysis will be performed in terms of the different time points (i.e., baseline, post-test, and 2-week follow-up) of the various groups (i.e., WBVBT, BT, WBV, and control group). A correlation analysis will be conducted to determine the relationship between changes in sensorimotor deficits and neural plasticity. To estimate the efficacy and effectiveness of interventions, per‑protocol and intention-to-treat analysis will be conducted respectively if any participants withdraw.

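### The listed inputs do not determine N=64, and the 80% power does not carry over to the planned one-way ANOVA (61% at 64 completers)

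*Protocol article*

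**What the plan says.** All references are to the protocol article, Methods.

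- **Sample size, effect size:** "The effect size is determined based on the value (0.35) previously reported in a study investigating cortical adaptations after balance training".
- **Sample size, other inputs:** "Other parameters in the software of G-power are α error (0.05), power (0.8), number of groups (4), and number of measurements (3").
- **Sample size, result:** "Based on the above parameters, the total sample size given by the software is 64". Then: "Considering a 20% dropout rate, a total of 80 participants will be included, with 20 in each group".
- **Statistics analysis, first comparison:** "A 1-way ANOVA analysis will be conducted to compare outcomes among the four groups".
- **Statistics analysis, second comparison:** "A 2-way repeated-measure ANOVA analysis will be performed in terms of the different time points (i.e., baseline, post-test, and 2-week follow-up"), crossed with the four groups.

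The Sample size section names no F test, no effect-size option and no correlation between visits. The Statistics analysis section does not say which of the two ANOVAs carries the conclusion. Under Randomization, allocation, and blinding, allocation comes after baseline testing.

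**The concern.** The article presents 64 as following from the inputs it lists. A four-group, three-visit design offers several F tests, and with the same 0.35 they need very different numbers. Without the name of the test, a reader cannot tell what the 80% power refers to.

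Two consequences follow. First, one of the two group comparisons the plan names, the one-way ANOVA, may have much less than 80% power, and a non-significant result from it could be read as stronger evidence against vibration than it is. Second, if the between-groups effect was sized, that effect averages all three visits. Baseline precedes randomisation, so the groups have no true difference there, and the average dilutes whatever effect the intervention has.

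**Working it through.** **Inputs.** From the article: effect size 0.35, alpha 0.05, target power 0.80, k = 4 groups, m = 3 measurements, N = 64, 20% dropout. Assumed because the article does not give them: 0.35 is Cohen's f (the scale that F-test routines take), sphericity holds, and the correlation between visits (rho) is 0.5, the software default, varied where shown. Power comes from the noncentral F distribution with noncentrality λ. N is a multiple of 4.

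**Step 1: which tests give 64?**

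| Test | λ | df at N | Smallest N for 80% | Power at 64 |
|---|---|---|---|---|
| Repeated measures, between groups, rho 0.5 | f²·N·m / (1 + (m−1)·rho) | 3, N−4 | **64** (60 gives 77.4%) | 80.5% |
| Group-by-time, 'as in SPSS' option | f²·(N−k)·(m−1) | 6, 2(N−4) | **64** (60 gives 77.7%) | 81.1% |
| Group-by-time, 'as in Cohen' option | f²·N·(m−1) | 6, 2(N−4) | 60 | 84.0% |
| Group-by-time, default option, rho 0.5 | f²·N·m / (1−rho) | 6, 2(N−4) | 24 | over 99.9% |
| One-way ANOVA at one visit | f²·N | 3, N−4 | 96 | 61.3% |

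Numbers for the two routes that reproduce the article's figure, with f² = 0.1225:

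- Between groups: λ = 0.1225 × 64 × 3 / 2 = 11.76 on 3 and 60 df, power 0.8045.
- Interaction, 'as in SPSS': λ = 0.1225 × 60 × 2 = 14.70 on 6 and 120 df, power 0.811. This route needs no correlation.

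The between-groups figure also moves with rho: N is 52 at rho 0.3 and 76 at rho 0.7.

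**Step 2: the one-way ANOVA.** At 64 completers, λ = 0.1225 × 64 = 7.84 on 3 and 60 df, power 61%. If all 80 complete, λ = 9.80 on 3 and 76 df, power 73%. For 80% it needs 96 completers, or 96 / 0.8 = 120 enrolled.

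**Step 3: dropout.** 64 / 0.8 = 80. This step is correct.

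**Step 4: what if 0.35 is the group separation at each visit after baseline, with none at baseline?** This is an assumption that the article neither states nor rules out.

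- Between-groups effect: the average over visits is (0 + 0.35 + 0.35) / 3 = 0.233, two-thirds of the post-baseline effect. At rho 0.5, λ = 0.233² × 64 × 1.5 = 5.23, power 43% (53% at rho 0.3, 34% at rho 0.8).
- Interaction: the visit pattern (0, 1, 1) centred is (−2/3, 1/3, 1/3), with mean square 2/9, so f = 0.35 × √(2/9) = 0.165. In the default form λ = 0.165² × 64 × 3 / (1 − rho). Power is 47%, 64%, 88% and 98% at rho 0.3, 0.5, 0.7 and 0.8.

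**Step 5: a baseline-adjusted comparison** at 64 completers, f = 0.35, 3 and 59 df.

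- Post-intervention visit: λ = f²·N / (1 − rho²). At rho 0.5 this is 7.84 / 0.75 = 10.45, power 75%. At rho 0.3 it is 7.84 / 0.91 = 8.62, power 66%. At rho 0.8 it is 7.84 / 0.36 = 21.78, power 98%.
- Mean of the two post-baseline visits: residual variance (1 + rho)/2 − rho². At rho 0.5 this is 0.75 − 0.25 = 0.50, λ = 7.84 / 0.50 = 15.68, power 91%. At rho 0.3 it is 0.65 − 0.09 = 0.56, λ = 14.00, power 87%.

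**The case against.** The strongest reply is that 64 may be correctly derived for the right test. The 'as in SPSS' interaction gives 64 without a correlation, the article lists no correlation, and the analysis section names SPSS and a two-way repeated-measures ANOVA. On the stated 0.35 that ANOVA keeps at least 80% power at 64 for the group effect at rho 0.5, and at least 81% for the interaction under each option in the table. This stands. A reader might infer that 64 can come only from the between-groups effect, so that the wrong test was sized. The documents do not support that.

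It is also fair to say that the 43% and the 47–98% in step 4 rest on a meaning of 0.35 that the article does not give. A range that crosses 80% does not show that the interaction lacks power.

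A full protocol might hold the missing settings, since an article condenses. But the article itself offers 64 as the result of the inputs it lists, and those inputs give 24, 60, 64 or 96 depending on the test.

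One could read the one-way ANOVA as a baseline comparability check, or as secondary to the two-way analysis. The text limits it to neither. It is planned for outcomes among the four groups, with no rank between the two analyses.

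**Conclusion.** The point holds in a limited form. N=64 does not follow from the listed inputs alone, and at least two different tests, using different definitions of 0.35, lead to it. The 80% power does not apply to the planned one-way ANOVA, which has 61% at 64 completers and 73% at 80. That result needs only the article's own figures, with 0.35 read as Cohen's f at the visit compared.

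The interaction reaches 80% if 0.35 is itself the interaction effect. If 0.35 is the separation at each post-baseline visit (an assumption), its power runs from about 47% to 98% for rho 0.3 to 0.8.

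Two stronger readings are tempting and should be resisted. One is that no planned test has 80% power; the two-way ANOVA does on the stated 0.35. The other is that the between-groups effect says nothing about benefit. It measures a diluted benefit, two-thirds of the post-baseline effect in the scenario shown.

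**What to change.** Keep N=80.

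1. **Sample size section:** state which F test, which effect-size definition and which correlation (if any) gave 64, and restate power for the one-way ANOVA: 61% at 64 completers and 73% at 80, for f = 0.35.
2. **Statistics analysis section:** replace the unadjusted one-way comparison with a group comparison adjusted for the baseline value already collected, and name it as the lead test. On the assumptions in step 5 (f = 0.35, rho 0.5, 64 completers), power rises from 61% to about 75% at the post-intervention visit, or to 91% if the outcome is the mean of the two post-baseline visits. State the assumed correlation, since the gain depends on it.

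The cost is a less favourable stated power for some tests and a small change to the analysis section. No extra participants, visits or measurements are needed.

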### Statistics analysis

As all outcomes are continuous variables, they will be presented as mean ± standard deviation. The normality of variables will be tested by the Shapiro–Wilk test. All statistical analyses will be carried out using the SPSS software (Version 22.0, IBM Corp., Armonk, NY, USA) and *p* < 0.05 will be considered as a significant difference. Bonferroni adjustment will be performed in post-hoc analysis when statistical significance is found. A 1-way ANOVA analysis will be conducted to compare outcomes among the four groups. Pearson's correlation coefficient will be calculated to evaluate the relationship between alterations in sensorimotor function and plastic changes in the brain. The effect size (Cohen’s d, 95% confidence intervals) will be calculated to evaluate the magnitude of difference among groups. Ranges 0.2–0.49, 0.5–0.79, and > 0.8 are considered as small, medium, and large effect sizes respectively. A 2-way repeated-measure ANOVA analysis will be performed in terms of the different time points (i.e., baseline, post-test, and 2-week follow-up) of the various groups (i.e., WBVBT, BT, WBV, and control group). A correlation analysis will be conducted to determine the relationship between changes in sensorimotor deficits and neural plasticity. To estimate the efficacy and effectiveness of interventions, per‑protocol and intention-to-treat analysis will be conducted respectively if any participants withdraw.

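### Plain Bonferroni for the post-hoc arm comparisons is valid but needlessly conservative; if the family is all six pairs, a step-down rule holds the same 5% family-wise error with slightly more power

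*Protocol article*

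**What the plan says.** The Statistics analysis section of the protocol article states the rule for comparisons that follow an overall test: "Bonferroni adjustment will be performed in post-hoc analysis when statistical significance is found". The next sentence names one overall test: "A 1-way ANOVA analysis will be conducted to compare outcomes among the four groups". Later in the same paragraph a second appears: "A 2-way repeated-measure ANOVA analysis will be performed in terms of the different time points", crossing three time points with the four arms. The section does not give the Bonferroni divisor, the comparisons that form the family, or which of the two overall tests opens the way to the post-hoc tests.

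The Sample size section supplies the planning effect ("The effect size is determined based on the value (0.35) previously reported"), with alpha 0.05, power 0.8, four groups and three measurements. It reports that "the total sample size given by the software is 64", which is 16 per arm, and raises this to 80, or 20 per arm, for 20% dropout.

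**The concern.** The first research question in the Background, whether vibration gives sensorimotor benefit, is answered by comparing particular arms. A significant four-arm F test does not say which arm differs, so the post-hoc rule decides what the trial can claim.

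Plain Bonferroni holds every pair to the threshold that is needed only when all six null hypotheses are true. Once one pair has been declared different, fewer nulls can remain true and the threshold can be relaxed without exceeding 5%. A single-step divisor of six gives this up. With 16 to 20 per arm the pairwise comparisons have little power to spare.

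**Working it through.** **Inputs.** From the article: alpha 0.05, four arms, f = 0.35, 64 participants before dropout (16 per arm), 80 enrolled (20 per arm). Assumed: all six pairs form the family; tests are two-sided with pooled variance; data are normal; f applies at a single visit.

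**The plan's own figure.** The between-factors repeated-measures formula is λ = f²·N·m / (1 + (m − 1)ρ). With m = 3 and an assumed ρ = 0.5 (not stated in the article), λ = 0.1225 × 64 × 3 / 2 = 11.76. Power on 3 and 60 degrees of freedom is 0.8045, so 64 is reproduced, and 64 / 0.8 = 80. A one-way test on a single measurement would need 96, so f = 0.35 is less favourable on the single-visit scale used below.

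**Number of pairs.** 4 × 3 / 2 = 6, and 0.05 / 6 = 0.0083.

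**Why step-down suffices.** With four arms the number of true pairwise nulls can only be 6, 3, 2, 1 or 0. Holm compares the ordered p-values with 0.05/6, 0.05/5, 0.05/4, 0.05/3, 0.05/2 and 0.05, stopping at the first failure. Shaffer uses the logical limit as well: after one rejection at most three nulls remain true, so the thresholds are 0.05/6, 0.05/3, 0.05/3, 0.05/3, 0.05/2 and 0.05. No threshold is below 0.05/6, so either rule rejects whatever plain Bonferroni rejects, with or without a gate.

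**Power at f = 0.35, 16 per arm** (simulated; per true pair in the first two rows, largest pair in the last two):

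| Pattern of means | d | Gate + Bonferroni/6 | Holm, no gate | One-way F gate + Shaffer from 0.05/3 |
|---|---|---|---|---|
| One arm different | 0.81 | 0.335 | 0.36 | 0.411 |
| Two against two | 0.70 | 0.235 | 0.26 | 0.308 |
| Evenly spaced | 0.94 | 0.469 | 0.49 | 0.529 |
| Extremes, two midway | 0.99 | 0.524 | 0.54 | 0.570 |

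At 20 per arm the gated Bonferroni and gated Shaffer figures are 0.443 and 0.526, 0.315 and 0.401, 0.597 and 0.654, and 0.651 and 0.693. Over both sample sizes Holm gains 1.6 to 3.3 points, ungated Shaffer about 3 to 6 (nearly 7 at most), and gated Shaffer about 4 to 9.

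**Cost of the gate alone** (16 per arm, Bonferroni/6 with and without it): 0.334 and 0.337; 0.237 and 0.239; 0.472 and 0.479; 0.525 and 0.536. That is 0.2 to 1.1 points.

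**Family-wise error.**
- Gate plus Bonferroni/6: 0.038 with all arms equal, 0.008 to 0.023 otherwise.
- Holm, and Shaffer behind a one-way gate: at most 0.050, apart from simulation noise, including patterns with arms far apart.
- One-way F gate with no further adjustment: about 0.12 with one arm different, about 0.10 with two against two.
- Thresholds starting at 0.05/3 with no effective gate at that visit and all arms equal: 0.074 to 0.078.

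**The case against.** The strongest reply is that an overall ANOVA followed by Bonferroni is standard and valid, that the article contradicts nothing here, and that a condensed article may leave the family and divisor to an analysis plan that is not shown. Most of this stands. No error rate is exceeded, and the unstated divisor is not itself a fault. What remains is that the article does name the adjustment method, and another method with the same guarantee rejects at least as much.

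A second reply is that the absolute powers above look low because f = 0.35 was placed on a single visit. That is also fair. On the scale of the mean of three measurements (ρ = 0.5), with one arm different and 16 per arm, the gated Bonferroni rule has power 0.531. The gain from a divisor of three is nonetheless similar there (0.617, or 8.6 points), so the scale changes the baseline more than the difference.

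Two stronger readings are tempting, and the documents support neither:
- A reader might infer that testing after a significant ANOVA and then applying Bonferroni pays for error control twice, so that the adjustment could be dropped. The gate costs at most about 1 point, and with four arms a significant F test alone lets family-wise error rise to about 12%. Some adjustment is needed.
- A reader might infer that 0.05/3 can always replace 0.05/6. That needs the gate to be the one-way ANOVA on the same outcome at the same visit. The article names a repeated-measures ANOVA too and does not say which is the gate. A repeated-measures effect can be significant because of another visit while all four arms are equal at the visit being tested.

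**Conclusion.** The point holds as a modest efficiency improvement. If the family is all six pairs, plain Bonferroni gives away about 2 to 3 points of power per comparison against Holm and about 3 to 6 against ungated Shaffer, at f = 0.35 with 16 to 20 per arm. Both alternatives are safe whichever overall test was meant as the gate. The larger gain of about 4 to 9 points is conditional on a one-way gate at the same visit, which the article does not fix. If a smaller family of comparisons was intended, the divisor and the gain would differ. Family-wise error here means error over the six pairs for one outcome at one visit.

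**What to change.** In the Statistics analysis section, replace the Bonferroni sentence with a rule that, for each outcome and within each visit, the six pairwise arm comparisons are adjusted by Holm's procedure at family-wise 0.05 and are not conditional on the omnibus test. Ungated Shaffer thresholds (0.05/6, 0.05/3, 0.05/3, 0.05/3, 0.05/2, 0.05) are an alternative with somewhat more power.

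If the gate is kept, name it. Only where it is the one-way four-arm ANOVA on the same outcome at the same visit may the first threshold be 0.05/3. That version must not follow a repeated-measures main effect or interaction.

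The cost is one sentence and a few lines of code outside the standard SPSS post-hoc menu; no participants or data are added. The small drawback is that step-down p-values have no matching simultaneous confidence intervals. The only intervals the section mentions are 95% intervals for Cohen's d, and it does not say whether they are meant to be simultaneous.

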**Methods:**

The present study is a single-blind randomized controlled trial. A total of 80 participants with CAI recruited from the university and local communities will be divided into 4 groups: whole-body vibration and balance training (WBVBT), balance training (BT), whole-body vibration (WBV), and control group. Participants will be given the WBV intervention (25-38 Hz, 1.3-2 mm, 3-time per week, 6-week) supervised by a professional therapist. Primary outcome measures are sensorimotor function including strength, balance, proprioception and functional performance. Brain plasticity will be evaluated by corticomotor excitability, inhibition, and representation of muscles, as measured by transcranial magnetic stimulation. Activation of brain areas will be assessed through functional near-infrared spectroscopy. Secondary outcome measures are self-reported functional outcomes involving the Cumberland Ankle Instability Tool and the Foot and Ankle Ability Measure. All tests will be conducted before and after the WBV intervention, and at 2-week follow-up. Per‑protocol and intention-to-treat analysis will be applied if any participants withdraw.

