Neuromuscular training, which usually refers to either proprioceptive drill, strength training, or a combination of both [23, 24], is an effective intervention modality in treating the sensorimotor deficits of individuals with CAI [25, 26]. However, it has not been fully determined as to which neurophysiological mechanism contributes the most to the benefits of neuromuscular training. Based on the existing hypothesis, the mechanism underlying the effect of neuromuscular training on sensorimotor deficits may be related to both spinal (e.g., altered H-reflex) and supraspinal adaptation (e.g., feed-forward reflexive mechanism) [4, 27, 28], yet relevant evidence is lacking for these hypotheses. As one form of neuromuscular training, whole-body vibration (WBV) has been widely studied in different areas such as sports [29], rehabilitation [30], and public health [31]. The possible mechanism of WBV benefits is that it could facilitate reflexive activation at both the spinal and supraspinal level in the central nervous system [32, 33]. To be specific, WBV has been shown to be capable of modulating spinal excitability in a human trial [34], and modulating synaptic plasticity [35, 36] and neurogenesis [37] in the brain of animals. Regarding the effectiveness of WBV for CAI, it has been found that additional benefits could be achieved in sensorimotor deficits (e.g., postural control, strength, and muscle activity) when WBV was added as a supplementary tool [38–40]. Nevertheless, it was still unknown whether the improvements in sensorimotor functions were associated with plastic changes in the brain for people with CAI. Investigation of the relationship between effectiveness of WBV and brain plasticity may provide understanding regarding the pathways through which WBV works on CAI [16].

Therefore, a single-blind randomized controlled trial will be designed to answer the following questions: (a) if WBV can generate sensorimotor benefits for patients with CAI? (b) is there a correlation between changes of sensorimotor functions and alterations of brain plasticity for participants with CAI? In this study, We hypothesize that there will be plastic changes in the brain after the WBV intervention, and these alterations will be correlated with changes in sensorimotor functions.

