### Outcome measures

Sociodemographic information including name, sex, age, dominant leg, physical activity and level of kinesiophobia will be collected through online questionnaires. Self-reported measures consist of the CAIT and FAAM. Objective measures in the current study include sensorimotor function and brain plasticity. The primary outcome measures will be balance with SEBT end-point to determine sensorimotor deficit, and activation of brain area with oxyhemoglobin in determining brain plasticity. All measures of outcome will be performed by a qualified blinded assessor, who is independent of the current study, at the fitness laboratory of Zhejiang University. An adequate rest period, assessed with a rating of perceived exertion (Borg scale, 6–20), will be given between each of the two objective measures to avoid potential fatigue. Since TMS is potentially associated with alterations of functional performance, the test orders (Table 2) will be arranged to mitigate any mutual influence between each two tests. To avoid the influence of myopia on balance control, participants will be asked to wear any corrective eyewear throughout the test process. The extremity with the lower CAIT score will be tested if bilateral ankle instability exists. Outcome measures will be assessed before and after the WBV intervention. According to a previous study, there were delayed improvements in balance and self-reported functions for patients with CAIafter accepting balance training programs [56]. Hence, the follow-up assessments will be performed 2-week after the intervention program.

**Table 2 Tab2:** SPIRIT timetable including schedule of enrolment, interventions and assessments

	Study period					
	Enrolment	Baseline assessment	Allocation	Post-allocation	Post-intervention assessment	Follow-up
Time points	-4 to -1 weeks		0	1–6 Weeks	6–7 weeks	8–9 Weeks
Enrollment						
Eligibility screen	X					
Informed consent	X					
Random allocation			X			
Intervention						
WBV						
Assessment						
Primary outcome measures						
Brain activity						
Corticomotor Plasticity (TMS)		X			X	X
Activation of brain area (fNIRS)		X			X	X
Sensorimotor deficits						
Balance (SEBT&TIBT)		X			X	X
Strength (HHD)		X			X	X
Proprioception (AMEDA)		X			X	X
Functional performance (SHT)		X			X	X
Secondary outcome measures						
Ankle instability (CAIT)		X			X	X
Ankle function (FAAM)		X			X	X

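### No deciding test, effect or visit is named for an outcome; if any of the planned between-group tests may decide, the per-outcome false-positive rate is roughly 10–15%, not 5%

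*Protocol article*

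**What the plan says.** The Statistics analysis section lists two omnibus analyses of the outcomes. First, "A 1-way ANOVA analysis will be conducted to compare outcomes among the four groups". The visit, and whether raw or change scores are used, are not given. Second, "A 2-way repeated-measure ANOVA analysis will be performed in terms of the different time points", the time points being baseline, post-test and 2-week follow-up, crossed with the four arms. That model yields a group, a time and a group-by-time F test. One threshold serves everything: p < "0.05 will be considered as a significant difference". The only multiplicity control is that "Bonferroni adjustment will be performed in post-hoc analysis when statistical significance is found".

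No visit is singled out elsewhere. The Abstract says "All tests will be conducted before and after the WBV intervention, and at 2-week follow-up". The Outcome measures section says "The primary outcome measures will be balance with SEBT end-point to determine sensorimotor deficit, and activation of brain area with oxyhemoglobin", with no time point attached. The Sample size section enters 4 groups and 3 measurements into G*Power but does not say which effect was powered. In the Background the hypothesis reads "We hypothesize that there will be plastic changes in the brain after the WBV intervention", and goes on to a correlation with sensorimotor change. It names no comparator arm.

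**The concern.** The candidate tests answer different questions. A one-way ANOVA at post-test looks at the immediate difference, and one at follow-up at the retained difference. The repeated-measures group effect averages over all visits, including the baseline measured before allocation. The interaction asks whether change over time differs between arms. They can disagree on the same data.

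A p-value below 0.05 on any of them could be reported as the effect of whole-body vibration with nothing in the text broken. The Bonferroni step does not help, because it starts only after an omnibus test is already significant. The problem is separate from how many outcomes there are: it remains after a single primary outcome is fixed.

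**Working it through.** **Inputs from the documents.** α = 0.05, 4 arms, 3 visits, effect size 0.35 (taken as Cohen's f), power 0.8, N = 64 before dropout and 80 after (16 and 20 per arm). **Assumed:** the between-visit correlation ρ, which the article does not give, and one-way ANOVAs at post-test and at follow-up.

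**Step 1. Does the sample size reveal the deciding test?** With k = 4, m = 3, f² = 0.1225:

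- Repeated-measures group effect: λ = f²·N·m / (1 + (m − 1)ρ). At N = 64, ρ = 0.5: 0.1225 × 64 × 3 / 2 = 11.76 on 3 and 60 df, power 0.805. N = 60 gives 0.774. So 64 is reproduced.
- Interaction, SPSS effect-size convention: λ = f²·(N − k)(m − 1) = 0.1225 × 60 × 2 = 14.7 on 6 and 120 df, power 0.811. N = 60 gives 0.777. So 64 is reproduced again.
- Interaction, G*Power default convention, ρ = 0.5: N = 24.
- One-way ANOVA at a single visit: N = 96.
- Dropout: 64 / (1 − 0.2) = 80, as stated.

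The figure 64 fits two different F tests, so it does not identify the deciding one.

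**Step 2. False-positive rate for one outcome.** Data were simulated with no effect: 4 arms, 3 visits, equal correlation between visits, ρ from 0.3 to 0.8, 16 or 20 per arm, 40,000 trials per setting. The rate is the share of trials with at least one p < 0.05 among the tests allowed to decide.

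| Tests that may decide | Rate |
|---|---|
| One named test (interaction, or one-way ANOVA at one visit) | about 5% |
| One-way ANOVA at post-test or follow-up | 8–10% |
| Repeated-measures group effect or interaction | 9–10% |
| Two one-way ANOVAs on change scores, or interaction | about 10% |
| Two one-way ANOVAs on raw scores, or interaction | 12–13% |
| Two one-way ANOVAs, interaction or group effect | 13–15% (about 14% at ρ = 0.5) |

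As a cross-check, two independent tests give 1 − 0.95² = 9.75%. The group effect and interaction are close to independent under equal correlation, and the simulation agrees. Three independent tests would give 1 − 0.95³ = 14.3%. The actual three-test rate is lower because the tests share data.

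**Step 3. Power if one visit is made to decide (N = 64, f = 0.35).**

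- Unadjusted: λ = 0.1225 × 64 = 7.84 on 3 and 60 df, power 0.61.
- Baseline-adjusted: f becomes 0.35 / √(1 − r²), where r is the correlation of baseline with the deciding visit. For r = 0.3, 0.5 and 0.7 this is 0.367, 0.404 and 0.490, and power is 0.66, 0.75 and 0.90.

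**The case against.** The one-way sentence is singular and names no visit. It could mean a baseline comparison or a supplement to the repeated-measures model. The Sample size section's three measurements point to a repeated-measures main analysis, which uses all visits jointly and needs no deciding visit. If its interaction alone decides, the rate is 5%. A condensed article may also leave such detail to an analysis plan that is not shown.

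Part of this stands. The documents do not support a flat 14%: that needs four tests, with a one-way ANOVA at each post-baseline visit, which the text does not state. The objection does not remove the point. The sentence speaks of outcomes, not baseline characteristics. Even with the one-way ANOVA set aside, the choice between group effect and interaction is open, and that alone gives 9–10%. Nor is this mere silence: the article itself fixes the tests, the threshold and the limited reach of Bonferroni.

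A reader might also infer, from the before-after wording of the hypothesis, that a time effect shared by all arms would be claimed as an effect of vibration. The documents do not say so: there is a no-intervention control and the analyses compare groups. The wording is loose and worth correcting, but no error rate can be attached to it. Likewise, the mention of delayed improvements in Outcome measures justifies scheduling a follow-up; it does not say that either visit may be taken as the result.

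**Conclusion.** The point holds in this form: several overlapping between-group tests are planned on each outcome at p < 0.05, none is named as deciding, and the stated multiplicity step does not cover the choice. If any of them may decide, the per-outcome rate is roughly 10–15%, depending on how many count. It is 5% only under a single named test.

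The range rests on the assumed correlation of 0.3–0.8, equal correlation between visits, and the assumed visits for the one-way ANOVA. Which tests are allowed to decide matters more than the correlation. The choice between per-protocol and intention-to-treat results was not counted. This should be corrected before analysis.

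**What to change.** In Statistics analysis, name one deciding between-group test for each primary outcome. Two options fit the design:

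1. The group-by-time interaction of the repeated-measures model. The 64 can then stand if the SPSS effect-size convention was the one meant; Sample size should say so.
2. A baseline-adjusted between-group contrast at one named visit, with the arms compared specified, from a single longitudinal model. The other visit is tested second, only if the first is significant.

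State that the one-way ANOVAs, the group main effect averaged over baseline, the time main effect and within-arm changes are descriptive. In the Background, word the hypothesis as a difference in change between arms.

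Cost: option 1 is wording only. Under option 2 a benefit seen only at the second-ranked visit is not confirmatory, and the power statement must be redone for the chosen test. As a guide, the four-arm single-visit test at N = 64 has power 0.61 unadjusted and 0.66–0.90 with baseline adjustment at assumed correlations of 0.3–0.7. Unless baseline correlates well with the deciding visit, option 2 may need more participants or a lower stated power.
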